**Case definition:**

**1) Symptomatic case:** Symptomatic COVID-19 infection defined as cough, dyspnea, fever, myalgia, arthralgia or rhinorrhea plus SARS Cov2 positive PCR.

**2) Asymptomatic case:** SARS Cov2 PCR in the absence of any symptoms potentially related to COVID19.

**3) Case cured:** IgG serology positive with SARS Cov2 negative PCR and absence of symptoms (this HP will be excluded, but gives valuable information on the prevalence of infection in HP).

**Study duration:** Twenty-five weeks, distributed as follows: 1) Recruitment period: Eight weeks from the inclusion of the first subject to the inclusion of the last study individual. 2) Screening period: After signing the informed consent, an IgG serology and coronavirus PCR will be performed, the result of which will be obtained in a maximum period of 7 days. After obtaining a negative result and corroborating a non-prolonged QTc interval, the study subject will start taking the corresponding medication. 3) Eight weeks of chemoprophylaxis vs placebo. 4) Eight weeks for database debugging and analysis of results. Preliminary publication of the first results.

**Questionnaire and variables to analyze.** Demographic data. Profession (assistant, technician, caretaker, nurse, doctor). Specialty and definition of the job. Follow-up of the recommendations (use of PPE, hand hygiene). Definition and history of the type of contact (s): 1) Close contact with possible, probable or confirmed case with required PPE use. 2) Close contact with possible, probable or confirmed case without use of required PPE. 3) Casual contact with possible, probable or confirmed case with the use of required PPE. Comorbidities (HT, DM, Smoker, Pulmonary, cardiac pathology). Pharmacological treatment at the time of inclusion in the study. Information about the COVID19 infection if it occurs (date of diagnosis). **Analytical evaluation:** Leukocyte count, platelets, hemoglobin, prothrombin activity, INR, urea, creatinine, glucose, cholesterol, HDL, LDL, AST, ALT, alkaline phosphatase, GGT, bilirubin, albumin, sodium, potassium, prothrombin rate, proteins totals, triglycerides, ferritin, uric acid, PCR. **Electrocardiogram. A sample for research** will be obtained at baseline and + 10 weeks, which will be transferred and stored in the Biobank for future research in the line of research; one of the samples will include DNA. **Clinical manifestations:** cough, odynophagia, fever, dyspnea, pleuritic pain, headache, diarrhea, anosmia, ageusia, others. **Severity:** qSOFA scale, CURB-65, evolution to ARDS, need for mechanical ventilation. Radiological manifestations. **Treatment** of the infection**. Evaluation of the adverse effects** of the administered medication**.**

**Main outcomes**The primary outcome of this study will be to evaluate:

Number and percentage of subjects presenting symptomatic and asymptomatic infection (see “Diagnosis of SARS CoV2 infection” below) by the SARS-Cov2 virus during the study observation period (8 weeks) in both treatment arms.

Number and percentage of subjects in each group presenting Pneumonia with severity criteria (Curb 65 ≥2) and number and percentage of subjects requiring admission to the Intensive Care Unit (ICU) in both treatment arms

# **Diagnosis of SARS CoV2 infection.** Determination of IgA, IgM and IgG type antibodies against SARS-CoV-2 using the Anti-SARS-CoV-2 ELISA kit (EUROIMMUN Medizinische Labordiagnostika AG, Germany) every two weeks. In cases of seroconversion, a SARS-CoV-2 PCR will be performed to rule out / confirm an active infection (RT-PCR in One Step: RT performed with mastermix (Takara) and IDT probes, following protocol published and validated by the CDC Evaluation of COVID-19 in case of SARS-CoV-2 infection.

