**4. Case definition:**

- **Symptomatic case:** Symptomatic COVID-19 infection defined as cough, dyspnea, fever, myalgia, arthralgia or rhinorrhea plus positive PCR-SARS-Cov2.

- **Asymptomatic case:** PCR-SARS-Cov2 positive in the absence of any symptoms potentially related to COVID19.

- **Case cured:** IgG serology positive with PCR-SARS-Cov2 negative and absence of symptoms.

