**Hydroxychloroquine. Reasons for choosing this drug.**

The reasons for the choice of HDQ over chloroquine is that it has shown increased activity against SARS CoV2 in vitro. The mechanism of action of HDQ with respect to SARS CoV2 infection is twofold, immunomodulatory, and antiviral. Its immunomodulatory capacity is largely due to the fact that it can increase intracellular pH and inhibit lysosomal activity in antigen-presenting cells, including plasmacytoid dendritic cells and B cells, thus preventing antigen processing and autoantigen presentation. class II mediated major histocompatibility complex to T cells (Lotteau V et al). This process reduces T cell activation, differentiation, and expression of costimulatory proteins and cytokines produced by T cells and B cells (Wu SF, et al / van den Borne BE, et al). Furthermore, due to altered endosome pH and disrupted binding between Toll-like receptors and their RNA / DNA ligands, TLR signaling is suppressed (Kuznik A et al / Ewald SE, et al), and thus interferes with the interaction between cytosolic DNA and the GMP-AMP synthase cyclic nucleic acid sensor (An J, Woodward JJ, et al). In this way, signaling activation decreases and cytokine production is attenuated, which justifies that HDQ could decrease the “cytokine storm”, a key phenomenon in the transition from mild to severe forms in COVID19. On the other hand, HDQ inhibits receptor binding and membrane fusion, two key steps required for cellular entry by coronavirus. It has been shown to exert an antiviral effect by interfering with the glycosylation of angiotensin-converting enzyme 2 (the cellular receptor for SARS-CoV2) and blocking the fusion of the virus with the host cell. Thus, virus binding to receptors in cells is prevented, and therefore infection is prevented. Following cell entry, HDQ concentrates on endosomes, Golgi vesicles, and lysosomes. The increase of the pH in the lysosome prevents the activity of the protease thus achieving that this fusion process is interrupted. Without the necessary pH for the endosome and lysosome to perform the excision function, coronavirus infection and replication are blocked

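### Seroconversion is the only written trigger for follow-up PCR, although every primary-outcome case needs a positive PCR; infections can be missed in both arms, possibly more often on hydroxychloroquine

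*Protocol*

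**What the plan says.** The primary outcome (Protocol, *Main outcomes*) begins "Number and percentage of subjects presenting symptomatic and asymptomatic infection" and refers the reader to *Diagnosis of SARS CoV2 infection* for how infection is established.

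That section sets one scheduled follow-up test, every two weeks: "Determination of IgA, IgM and IgG type antibodies against SARS-CoV-2 using the Anti-SARS-CoV-2 ELISA kit". It then gives one trigger for viral PCR: "In cases of seroconversion, a SARS-CoV-2 PCR will be performed to rule out / confirm an active infection".

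The *Case definition* sections require a positive PCR for both case types:
- Symptomatic: "Symptomatic COVID-19 infection defined as cough, dyspnea, fever, myalgia, arthralgia or rhinorrhea plus SARS Cov2 positive PCR".
- Asymptomatic: "PCR-SARS-Cov2 positive in the absence of any symptoms potentially related to COVID19".

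A third category, the cured case, is "IgG serology positive with SARS Cov2 negative PCR and absence of symptoms (this HP will be excluded". The note on exclusion shows that it was written chiefly with screening in mind. A participant with this profile during follow-up meets neither counted definition.

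The only PCR planned for everyone is at screening (*Study duration*): "After signing the informed consent, an IgG serology and coronavirus PCR will be performed".

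On mechanism, *Hydroxychloroquine. Reasons for choosing this drug* says the drug interferes with antigen processing in antigen-presenting cells, B cells among them, and with class II presentation to T cells. It adds: "This process reduces T cell activation, differentiation, and expression of costimulatory proteins and cytokines produced by T cells and B cells".

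**The concern.** The case definitions rest on PCR, but the follow-up schedule reaches PCR only through antibody. An infected participant who does not seroconvert by the last ELISA, or who has cleared the virus by the time antibody appears, is not counted. That is a loss of cases in both arms.

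The further concern is that the trigger may not be neutral between arms. Antigen presentation and T- and B-cell signalling lie upstream of an antibody response, and the protocol names them as targets of the active drug. If the drug blunted or delayed seroconversion, fewer PCRs would be triggered on active treatment, or they would come later and be negative more often. The active arm would then show fewer cases at the same true infection rate. Blinding would not prevent this, because the difference would be biological, and it could arise with no antiviral effect at all. The error would favour a claim of prevention on the primary endpoint, and no analysis can recover an infection that was never sampled.

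**Working it through.** **Step 1. Is any other PCR trigger written?** Reading the sections together:
- *Study duration*: PCR at screening only.
- *Diagnosis of SARS CoV2 infection*: PCR after seroconversion.
- *Case definition*: requires PCR but does not say when a symptomatic participant is swabbed.
- *Questionnaire and variables to analyze*: records the date of diagnosis, but sets no viral testing. The bare abbreviation PCR in its laboratory list stands among blood chemistry items and gives no viral schedule.

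No PCR triggered by symptoms or contact, scheduled during follow-up, or taken at end of treatment is written.

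**Step 2. Inputs for an illustration.** The protocol states no figure for detection, so there is none to reproduce.
- Infection risk: 15%, from *Sample size estimation*, applied to both arms (no true drug effect).
- Evaluable per arm: 225 less 5% dropout, 225 × 0.95 = 213.75, taken as 214.
- Test: pooled two-proportion test at two-sided 5%, counting only rejections that favour the drug. The probability is summed exactly over both binomial distributions.
- Assumptions not in the documents: r, the detection of antibody-dependent infections on active relative to placebo; and c, the share of infections found whatever the serology. Everything is detected on placebo unless stated.

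**Step 3. Formula.** Observed placebo rate = 15%. Observed active rate = 15% × [c + (1 − c) × r].

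Example, c = 0 and r = 0.8: 15% × 0.8 = 12.0%. Example, c = 0.5 and r = 0.8: 15% × (0.5 + 0.4) = 13.5%.

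**Step 4. Results.**

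| r | Active rate, c = 0 | False result for drug, c = 0 | Active rate, c = 0.5 | False result for drug, c = 0.5 |
|---|---|---|---|---|
| 1.0 | 15.0% | 2.5% | 15.0% | 2.5% |
| 0.9 | 13.5% | 6.4% | 14.25% | 4.1% |
| 0.8 | 12.0% | 14.6% | 13.5% | 6.4% |
| 0.7 | 10.5% | 28.6% | 12.75% | 9.9% |

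A normal approximation for c = 0, r = 0.8 agrees. The pooled rate is 13.5%, so the null standard error is √(2 × 0.135 × 0.865 / 214) = 0.0330; the unpooled one is also 0.0330. Then Φ((0.030 − 1.96 × 0.0330) / 0.0330) = Φ(−1.05), about 14.6%.

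**Step 5. Sensitivity to full placebo detection.** With c = 0 and only 70% detected on placebo, the observed placebo rate is 10.5%. At r = 0.9, 0.8 and 0.7 the chances are 5.4%, 11.0% and 20.3%. The c = 0 column in Step 4 is therefore a worst case for each r.

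**The case against.** The strongest case on the other side has four parts.

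1. **The drug link is inferred.** A reader might take the mechanism section to say that hydroxychloroquine suppresses antibody production. It does not. It describes antigen presentation, T-cell activation and cytokines, and goes on to the cytokine storm. *Hypothesis and expected results* treats reduced severity at this dose as less likely, though plausible, which is some reason not to presume a strong immunological effect. Nothing in the document says whether this dose would change a positive or negative ELISA result. This stands: the between-arm bias is a possibility, not a documented effect.

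2. **Delay is not loss.** ELISA is repeated every two weeks, so a late response can be caught at a later visit. *Background* says virus can persist for days or weeks after symptoms, so a later PCR may still be positive. This stands in part. Cases are still lost if seroconversion is absent, if infection comes late in the eight weeks, or if virus has cleared before the PCR.

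3. **Symptomatic staff may be swabbed anyway.** The symptomatic definition has no antibody condition, and the protocol collects date of diagnosis, clinical features and severity. So a reader should not infer that every infection depends on seroconversion. This narrows the point, and the gap is firmest for asymptomatic infection. It does not close it: the protocol nowhere says that routine-care PCR results count toward the primary outcome.

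4. **The largest figures are a worst case.** This stands. The 28.6% is not an expected error rate; it needs r = 0.7, no clinical detection and full detection on placebo.

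Nor is this simply detail to be left to an analysis plan. Which samples are taken, and when, has to be settled before data collection.

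**Conclusion.** The point holds as a defect in case ascertainment. The written route makes seroconversion a precondition for the PCR that defines a case, so infections can be missed in both arms, most clearly asymptomatic ones, which the main objective expressly includes.

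A larger loss on hydroxychloroquine, biasing toward apparent prevention, is plausible from the protocol's own account of mechanism, but it is an inference. Neither its existence nor its size is documented. Over the assumed range of r from 0.9 to 0.7, the chance of a false result favouring the drug is 6.4% to 28.6% if every infection depends on seroconversion, and 4.1% to 9.9% if half do not, against a nominal 2.5%. The documents do not support the stronger conclusion that the trial will falsely show efficacy.

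Should-fix: the endpoint is primary and the gap cannot be repaired after follow-up, but the between-arm part is unproven.

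**What to change.** In *Diagnosis of SARS CoV2 infection*:
- Add a SARS-CoV-2 PCR for any participant who develops a symptom listed in *Case definition*, whatever the serology. Name that list explicitly, because the clinical manifestations under *Questionnaire and variables to analyze* differ from it.
- State that hospital or occupational-health PCR results count toward the primary outcome.

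In the analysis text:
- Pre-specify PCR-confirmed symptomatic infection as a supportive analysis.
- Report primary-outcome cases by arm and detection route: symptom-triggered or clinical PCR versus seroconversion-triggered PCR.
- State as a limitation that asymptomatic detection still depends on antibody response, so a difference confined to seroconversion-triggered cases should be interpreted with caution.

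Symptom-triggered PCR does not remove the dependence for asymptomatic infection, which is why the split by route and the stated limitation are needed as well.

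Cost: protocol wording and some extra PCRs. The supportive analysis will have fewer events than the primary one and so less precision.

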**Background**

On December 31, 2019, the Wuhan Municipal Health and Sanitation Commission reported on a group of 27 cases of pneumonia of unknown etiology. On January 7, 2020, a new type of virus in the Coronaviridae family, SARS-CoV-2, was identified as causing this outbreak. This coronavirus has a high capacity for dissemination in hospitals, which is why health professionals have a high risk of SARS CoV2 infection as evidenced by data published in China (3,300 in early March) and estimates in Spain (about 10,000 at this time, which represents about 15% of the total registered cases, official data from the Ministry of Health). This high transmission capacity of this virus is not surprising if we consider the experience during the 2002 outbreak of severe acute respiratory syndrome (SARS), where 1,725 ​​of the health professionals (HP) were infected (Hsin DH, et al, Zou What's up.). In fact, there are several reasons that explain this high transmissibility: 1) people with a COVID19, are contagious from the beginning of the disease, that is, in the presymptomatic period, 2) the presence of the virus persists days or even weeks after disappearance of symptoms (Roman Woelfel et al.), 3) hyper-affinity to angiotensin-converting enzyme 2 receptors, causing high transmissibility, 4) false negatives, relatively common with standard techniques, 5) difficulty in establishing adequate screening circuits and in-hospital traffic (Clin Infect Dis (2020 March 12), 10.1093 / cid / ciaa255, 6) the high probability that the number of asymptomatic patients is much higher than currently admitted (R. Li et al ), 7) the difficulty in accessing adequate personal protective equipment (PPE) at times of extremely high incidence peaks, such as the current one, despite the priority given to teachers Most exposed professionals, 8) work in areas where aerosols are formed (Li Ran et al), poor hand hygiene (Lu W, et al. Sharma A, et al) and long working hours (Li D, Wu et al, Weaver MD, et al) are associated with an increase in infection in HP; and, 9) Finally, the saturation of health systems, with specific increases that may exceed 200% of normal activity, may influence this high in-hospital transmission of SARS CoV2.

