**Efficacy of HDQ against coronavirus.** HDQ is a powerful SARS CoV inhibitor, as demonstrated years ago (Vincent et al). Most of the results are preclinical, with direct evidence of very discreet efficacy at this time. A systematic review of the efficacy and safety of chloroquine shows that preclinical and long-term safety data support the use of this drug or perhaps better HDQ in clinical trials of prophylaxis and treatment in patients with COVID19 (Cortegiani A et al. to the.). Similarly, Liu et al, publish preliminary results showing that HDQ effectively inhibits SARS-CoV-2 infection in vitro. (Liu J et al). Preliminary reports from China, South Korea, and France suggest that the treatment is at least effective in some patients. In the only clinical trial, and even though it suffers from many objectionable points, 20 patients treated with 600 mg of HDQ daily (with or without adding azithromycin) were included in a single arm trial. The treated cases showed a significant reduction in the viral load compared to the controls and a clearly shorter average duration of the disease than the untreated subjects (Gautret et al). Chinese researchers reported that treatment in more than 100 chloroquine patients was beneficial (BioScience), but the data has not yet been published. In fact, information about HDQ's effectiveness in China is proving difficult to obtain. At this time, there are a plethora of clinical trials with no results available to date. Only one ongoing trial is evaluating the role of post-exposure chemoprophylaxis.

With the aforementioned data and in the context that, in the best of cases, a vaccine will not be had before 12-18 months, the prevention of infection in HP must be an absolute priority of our healthcare system. It is evident that an optimized screening and patient traffic in hospitals (Yen MY et al), the use of PPE whenever required and extreme precautionary measures should be the axis of prevention of transmission of infection to HP . But all these measures, with the limitations existing in our country, have not demonstrated a clear efficacy in preventing SARS CoV2 infection in our professionals. For this reason, we propose this clinical trial to evaluate the safety and efficacy of HDQ chemoprophylaxis of SARS CoV2 infection in HP in the hospital setting.

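### The case definitions count an infection only by PCR, the only follow-up PCR stated comes after seroconversion, and no rule says whether a PCR-negative seroconverter is a primary event

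*Protocol*

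**What the plan says.** **Primary outcome** (Protocol, Main outcomes): "Number and percentage of subjects presenting symptomatic and asymptomatic infection" over 8 weeks in each arm. The sentence refers the reader to the diagnosis section, not to the case definitions.

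**Case definitions.** The methodology section defines a symptomatic case as "Symptomatic COVID-19 infection defined as cough, dyspnea, fever, myalgia, arthralgia or rhinorrhea plus SARS Cov2 positive PCR". The summary's Case definition section defines an asymptomatic case as "PCR-SARS-Cov2 positive in the absence of any symptoms potentially related to COVID19". The methodology version of the asymptomatic line names PCR but omits the word positive. A third category, the cured case, reads "IgG serology positive with SARS Cov2 negative PCR and absence of symptoms (this HP will be excluded".

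**Testing on study** (Diagnosis of SARS CoV2 infection): IgA, IgM and IgG by ELISA ("EUROIMMUN Medizinische Labordiagnostika AG, Germany) every two weeks"), and then "In cases of seroconversion, a SARS-CoV-2 PCR will be performed to rule out / confirm an active infection". The only other coronavirus PCR stated is the one at screening, before treatment. No PCR prompted by symptoms or fixed to a visit is stated.

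**Relevant background.** Among its reasons for high transmissibility the protocol lists "false negatives, relatively common with standard techniques". Of an earlier treatment study it says "The treated cases showed a significant reduction in the viral load compared to the controls".

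**The concern.** The main objective is to prevent symptomatic and asymptomatic infection. The trial's own serology will identify people who were IgG-negative at screening and later seroconvert. If a PCR taken after that point decides whether they count, infections that have already cleared, or that PCR misses, drop out of the numerator.

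Two things are at stake. If the loss is equal in both arms, there are fewer events and less power. If the drug shortens PCR positivity without preventing infection, fewer treated seroconverters will still be positive when tested, and the arms will differ on the primary outcome although equal numbers were infected. In addition, if the exclusion attached to the cured category were applied after randomisation, participants would be removed because of something treatment can affect.

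**Working it through.** **Step 1: follow one participant through the text.** Take someone IgG- and PCR-negative at screening who becomes IgG-positive at a two-weekly sample and whose triggered PCR is negative.
- Symptomatic case: not met, since a positive PCR is required.
- Asymptomatic case: not met, since the summary's definition requires a positive PCR.
- Cured case: met if symptom-free. With symptoms, no category fits.
- Diagnosis section: seroconversion is detected and PCR settles whether infection is active. The section does not say whether infection that is no longer active counts.

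The case definitions therefore leave this participant uncounted, while the diagnosis section permits the opposite reading.

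**Step 2: inputs for size.** The Sample size section gives a 15% control risk, an 8-point difference (so 7% on treatment), two-sided 5% and 5% dropout. The design section gives 225 per arm, so 225 × 0.95 = 213.75, taken as 214. The share of infections still PCR-positive when tested is not given and is an assumption throughout. The sample size section states both 450 in total and 250 per arm. Its two-sided inputs give 237 per arm (unpooled variance), and 237 / 0.95 rounds up to 250; they do not give 225. That is a separate point. The arm size of 225 is used here because it is what the design section states.

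**Step 3: method.** Counted risk = infection risk × share PCR-positive. Test: z = (p1 − p2) / √(2p̄(1 − p̄)/n), without continuity correction, rejecting if |z| > 1.96. The rejection probability is the exact sum over two binomials with n = 214.

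Reference case, 15% vs 7%: exact power 76%. As a check by normal approximation, p̄ = 0.11, 1.96 × √(2 × 0.11 × 0.89/214) = 0.0593 and √((0.1275 + 0.0651)/214) = 0.0300. Then (0.08 − 0.0593)/0.0300 = 0.69, which gives power of about 75.5%.

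**Step 4: equal loss in both arms, true risks 15% and 7%.**

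| Share PCR-positive | Counted risks | Power |
|---|---|---|
| 100% | 15.0% vs 7.0% | 76% |
| 80% | 12.0% vs 5.6% | 65% |
| 50% | 7.5% vs 3.5% | 44% |

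**Step 5: no prevention, 15% infected in both arms, PCR positivity lower on the drug.**

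| Share positive, placebo vs drug | Counted risks | Significant at two-sided 5% |
|---|---|---|
| 70% vs 70% | 10.5% vs 10.5% | about 5% |
| 70% vs 60% | 10.5% vs 9.0% | 8% |
| 70% vs 50% | 10.5% vs 7.5% | 19% |
| 70% vs 35% | 10.5% vs 5.25% | 52% |

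**The case against.** The strongest reply is that the primary outcome refers to the diagnosis section, which begins with serology and uses PCR to separate active from past infection. On that reading seroconversion itself is the diagnosis and nothing is lost. The reading is possible, so a reader may not infer that the trial certainly discards these infections. But the diagnosis section never says that seroconversion counts, and the case definitions say otherwise. A primary endpoint open to both readings still needs settling.

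A reader might also infer that randomised participants will be dropped because of their outcome. The documents do not establish that. The first exclusion criterion uses almost the same words as the cured category, and the accompanying remark about prevalence suits a screening finding. What stands is that the category is not limited to screening.

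Nor does every seroconversion show infection on treatment. Screening results may take up to 7 days, and participants must have worked in high-exposure areas for the previous two weeks, so an early seroconverter may have been infected before the first tablet.

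The magnitudes have limits as well:
- The protocol says virus can persist for days or weeks after symptoms, which limits the loss.
- It does not bar counting a PCR done in routine care, so applying the loss to every infection may be too harsh.
- The 15% comes from registered cases, so discounting it may count under-detection twice.
- The viral-load evidence comes from a treatment study at 600 mg daily, which the protocol itself criticises; this trial uses 200 mg.

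These points weaken the figures, not the gap in the definition.

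**Conclusion.** The concern holds as a conflict over what counts as a primary event. Under the case definitions, an on-study IgG seroconverter with a negative PCR is not counted, although the main objective covers that infection. Under a permissible reading of the diagnosis section, the same person is counted.

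On the PCR-only reading, power falls and a pure effect on the duration of PCR positivity could pass for prevention. How far is unknown. The results in the two tables depend on assumed PCR-positive shares that the documents do not supply, on 15% being a true infection risk, and on all detection running through the seroconversion trigger. A small difference in clearance (70% vs 60%) moves the rejection rate only from 5% to 8%; the large figures need large differences. The documents do not support a claim that the trial is biased by any particular amount.

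**What to change.** In both Case definition sections, in Main outcomes and in Diagnosis of SARS CoV2 infection, use one definition of the primary event: any positive SARS-CoV-2 PCR after randomisation, from any source, or IgG seroconversion from a negative screening IgG whatever the PCR shows. IgG is the class to use, because it is the only one with a stated screening baseline.

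- Confirm seroconversion by repeat ELISA on the same or the next available sample. Requiring the next scheduled sample would leave week-8 conversions unconfirmed.
- Limit the cured-case exclusion to screening, and keep all randomised participants in the denominator.
- Report PCR-confirmed infection as a supportive outcome, and show the PCR and serology components separately.
- Add a sensitivity analysis without seroconversions at the first follow-up sample, since these may reflect infection before treatment.

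The cost is mainly wording plus some repeat ELISAs, because the two-weekly serology is already planned. There are two downsides. Some ELISA false positives will count. The drug may also affect antibody response, since the protocol's rationale says it impairs antigen presentation, including in B cells, and reduces T-cell activation. Reporting both components separately lets a reader see whether either one drives the result.
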